# Evaluation of two vaginal, uterus sparing operations for pelvic organ prolapse: modified Manchester operation (MM) and sacrospinous hysteropexy (SSH), a study protocol for a multicentre randomized non-inferiority trial (the SAM study)

**DOI:** 10.1186/s12905-019-0749-7

**Published:** 2019-04-02

**Keywords:** Sacrospinous hysteropexy, Modified Manchester operation, Uterine descent, Pelvic organ prolapse, POP-Q, Reconstructive surgery, Randomized clinical trial, Cost-utility

## Abstract

**Background:**

Pelvic organ prolapse (POP) affects up to 40% of parous women which adversely affects the quality of life. During a life time, 20% of all women will undergo an operation. In general the guidelines advise a vaginal operation in case of uterine descent: hysterectomy with uterosacral ligament plication (VH), sacrospinous hysteropexy (SSH) or a modified Manchester operation (MM). In the last decade, renewed interest in uterus sparing techniques has been observed. Previous studies have shown non-inferiority between SSH and VH. Whether or not SSH and MM are comparable concerning anatomical and functional outcome is still unknown. The practical application of both operations is at least in The Netherlands a known cause of practice pattern variation (PPV). To reveal any difference between both techniques the SAM-study was designed.

**Methods:**

The SAM-study is a randomized controlled multicentre non-inferiority study which compares SSH and MM. Women with symptomatic POP in any stage, uterine descent and POP-Quantification (POP-Q) point D at ≤ minus 1 cm are eligible. The primary outcome is the composite outcome at two years of absence of prolapse beyond the hymen in any compartment, the absence of bulge symptoms and absence of reoperation for pelvic organ prolapse. Secondary outcomes are hospital parameters, surgery related morbidity/complications, pain perception, further treatments for prolapse or urinary incontinence, POP-Q anatomy in all compartments, quality-of-life, sexual function, and cost-effectiveness. Follow-up takes place at 6 weeks, 12 and 24 months. Additionally at 12 weeks, 6 and 9 months cost-effectiveness will be assessed. Validated questionnaires will be used and gynaecological examination will be performed. Analysis will be performed following the intention-to-treat and per protocol principle. With a non-inferiority margin of 9% and an expected loss to follow-up of 10%, 424 women will be needed to prove non-inferiority with a confidence interval of 95%.

**Discussion:**

This study will evaluate the effectiveness and costs of SSH versus MM in women with primary POP. The evidence will show whether the existing PPV is detrimental and a de-implementation process regarding one of the operations is needed.

**Trial registration:**

Dutch Trial Register (NTR 6978, http://www.trialregister.nl). Date of registration: 29 January 2018. Prospectively registered.

## Background

Pelvic organ prolapse (POP) is a frequently diagnosed health problem in women which negatively affects the quality of life. 40% of vaginally parous women have at least stage 2 POP [1, 2]. In the Netherlands, 20% of all women will undergo POP surgery during life time [3, 4]. According to the current guidelines, the first choice surgical treatment is a vaginal POP operation [5]. When undergoing surgery these women have a 5–30% risk on re-operation due to recurrence [2, 6]. According to a nationwide Dutch registration (Kiwa Carity), 15,000 vaginally POP procedures are performed each year in the Netherlands [7]. Currently, three types of vaginal operations for uterine descent are performed the most; the vaginal hysterectomy (VH), the modified Manchester operation (MM) and the sacrospinous hysteropexy (SSH), all combined with colporrhaphy when indicated. SSH and MM are uterus preserving techniques in which the uterus is attached to different pelvic ligaments. The number of uterus sparing operations (SSH and MM) has increased more than fivefold between 1997 and 2009 in the Netherlands, at the expense of VH [8]. Still the three surgical treatments co-exist without solid evidence-based literature on comparison, which leads to practice pattern variation (PPV) between hospitals and gynaecologists. PPV is defined as a difference in care that cannot be explained by the underlying medical condition [9]. For example, in the Netherlands choice of treatment is more or less equally divided between the three procedures for women with stage two uterine descent (varying from 25 to 34%) [7, 8]. This indicates a situation of maximal practice pattern variation. The choice of treatment is dictated by the physician’s preference or skills and is (probably) not evidence based. Theoretically, PPV can lead to increased health costs. Additionally, the lack of evidence makes it more difficult to come to a process of shared decision making between doctor and patient and individually tailored management in this field.

First steps have been made in filling the knowledge gap; the comparison VH versus SSH has been made in several studies [10–12], and was well established by the SAVE-U randomized multicentre trial [13]. The latter showed equal effectiveness, but shorter operation times in SSH. In case of patient’s preference for uterus preservation [14], the SAVE-U publications have provided arguments to choose for uterus sparing surgery. Recently published systematic reviews by Kapoor et al. and Meriwether et al. confirmed these findings and additionally less blood loss was reported favouring uterus sparing surgery [15, 16]. Unlike these results, the systematic review by de Oliveira et al. showed a lower reoperation rate after VH. However, this review focused on more advanced uterine prolapse (at least stage II, POP-Q point C > 1 cm) [17].

The Manchester operation was first described in 1888 and has since gained ground in urogynaecology. Originally, the operation was a combination of a cervix amputation with anterior colporrhaphy [18]. Later, the cardinal ligaments were plicated and attached to the cervical stump and today the modern version of the operation is applied in which the sacro-uterine ligaments are plicated as well. Despite the scarcity in studies comparing the MM to other operating techniques, a recent historical cohort study by Tolstrup et al. showed superiority of MM compared to VH [19]. In addition, a recent prospective cohort study showed that the MM provides adequate mid-compartment support and gives excellent subjective results after one-year follow up [20].

It is thought that in case of an elongated cervix, MM may be more suitable than SSH. On the other hand, MM may lead to cervical stenosis (menstrual obstruction, poor access for diagnostics) which was reported up to 11% [21]. At the same time, previous studies have shown that SSH can be performed with a reduced operating time of approximately 19 min compared to MM (SSH 59 ± 13 min vs. MM 78 ± 28 min) [22, 23].

Uterine descent stage 3 is generally not treated with MM (but with VH or SSH), which was also seen in a cohort study on MM [24]. Although MM is performed approximately 3000 times a year in the Netherlands, still little is known about the effectiveness compared to SSH.

To our knowledge, most publications on MM and SSH for treatment of POP are based on observational studies. Only one recently performed randomized clinical trial compared the techniques, but contradictive to our design, women with uterine prolapse all underwent hysterectomy [25]. A randomized clinical trial comparing the SSH and MM with preservation of the uterus has not yet been performed. The PPV, women’s preference and upcoming trend towards uterus preserving surgery makes it inevitable to further fill the knowledge gap. This study will provide answer to the question: Is SSH non-inferior to MM in women with signs and symptoms of POP?

## Methods/design

### Study objectives and hypothesis

The objective of this study is to compare the effectiveness of SSH and MM in the treatment of uterine prolapse with POP-Q point D ≤ minus 1 cm. Comparison will be made concerning anatomy, symptoms, re-interventions, POP-recurrence, complications, hospital parameters, pelvic floor dysfunction, quality of life and costs with a follow-up of two years. Based on the current literature, it is hypothesized that both techniques are comparable regarding effectiveness, that is to say the composite outcome of recurrent anatomical POP with complaints or reoperation or pessary therapy.

### Study design

The SAM study is a multicentre, prospective, randomized, open-label clinical trial aimed at assessing the non-inferiority of the effectiveness of SSH compared to MM. This protocol was developed according to the Standardized Protocol Interventions: Recommendations for Interventional Trials (SPIRIT) 2013 statement [26].

### Study population, recruitment and consent

Women aged 18 or older who are eligible for their first surgical treatment for symptomatic pelvic organ prolapse in any stage and with uterine descent and POP-Q point D at ≤ minus 1 cm will be eligible for the study. We do not consider MM to be the appropriate treatment for women with POP-Q point D > minus 1 cm, since we believe that beyond that point the sacro-uterine ligaments will not provide substantial support. In that case, the patient would benefit more from an SSH. Patients with concomitant anterior or posterior wall prolapse will be included.

Women who underwent previous prolapse or other pelvic floor surgery, need concomitant mid-urethral sling surgery, have a wish or need for uterus removal, have a contraindication for uterus preservation (i.e. abnormal endometrial bleeding, endometrial or cervical malignancy), have a future wish for childbearing, have inadequate skills in the Dutch language or are not capable of filling in questionnaires will be excluded from the study. In case indicated, a pap-smear and/or pipelle endometrial biopsy must be normal before inclusion.

Participating centres will be 27 Dutch university, teaching and non-teaching hospitals (a list of participating centres is available at: http://zorgevaluatienederland.nl/sam). The SAM study is affiliated with the Dutch Consortium for Healthcare Evaluation and Research in Obstetrics and Gynaecology, which gives national attention and therefore ensures the right amount of participating hospitals to achieve adequate patient enrolment. Gynaecologists and trainees of all participating hospitals will perform the eligibility assessment. Eligible patients will be counselled about the study, the two operating techniques and follow-up. All patients will be provided written patient information which contains information about the aim of the study, follow-up, advantages and disadvantages. Patients will be given a week to make their decision on participation in the study. Women who agree to participate will be asked to sign written informed consent. The informed consent form will be obtained and signed by the investigator before randomisation. The rules of Good Clinical Practice will be applied.

All eligible patients who are counselled will be registered during inclusion period. From patients who do not want to participate, only reasons for refusal will be registered. All serious adverse events will be reported to the Medical Ethics Committee. Patient enrolment en recruitment is currently ongoing. 3 July 2018 the first patient enrolled the study. Enrolment is expected to conclude August 2020.

### Intervention

SSH: after opening the posterior vaginal wall, the pararectal space is explored at the right side and the sacrospinous ligament is identified. The posterior side of the cervix is attached to the sacrospinous ligament with two non-absorbable size 1 or 0 sutures at least 2 cm medial of the ischial spine. Either this procedure is performed open or using the Capio suturing device.

MM: the procedure consists of extraperitoneal plication of the uterosacral ligaments (and cardinal ligaments where possible) with use of three or four absorbable size 1 sutures and amputation of the cervix. The most cranial suture is fixated through the posterior fornix of the vagina.

In view of substantial variation in operative skills and experience there will be attention to avoid the measurement of learning curve effects in the study. Only centres where both techniques are performed before the start of the study or where mentoring/supervision is organised can participate in the study. All participating gynaecologists must have performed at least one hundred POP procedures, twenty procedures of each technique of which ten performed in the last three years before the beginning of the study. Before the study started, all participating gynaecologists were invited to a master class to discuss all steps of both procedures, to minimize practice variation. Agreement was reached by all participating gynaecologists. One uniform operation report for each procedure was written after these master classes and is used during the study. Only a few steps of the operation will be left to the preference of the gynaecologist, namely: application and type of hydrodissection, manner of cervical amputation and use of scalpel or scissors for opening the vaginal wall. All these steps will be registered. Allocated interventions will only be modified or discontinued in case the operating gynaecologist believes this is necessary during operation. This will be registered.

Anaesthesia will be either general or spinal, depending on the anaesthesiologist and patient preferences. Antibiotics will be given peri-operatively according to the hospital protocol. Bladder catheterisation will be done before operating one-off or with an indwelling catheter. After operation an indwelling catheter must remain in the bladder until the next morning. Urinary retention after removal will be reported. For both procedures anterior and/or posterior colporrhaphy will be performed as indicated.

### Outcome measures

The primary outcome will be success after two years follow-up. Success is defined as the absence of POP beyond the hymen in any compartment (POP-Q, gynaecological examination), the absence of bulge symptoms (absence of bulge symptoms is defined as a negative response to the question, “Do you see or feel a bulge in the vaginal area” (UDI domain genital prolapse score: 0)), and absence of reoperation or pessary therapy for POP [27].

Secondary outcomes of the study will be clinical parameters (surgery time, hospitalisation time), surgery related morbidity/complications (including menstrual problems, hematometra, any problems with uterine access such as diagnostic cervical or endometrial sampling or IUD insertion), pain perception, further treatments for POP or urinary incontinence, anatomy in all compartments using POPQ [28], general quality of life, disease specific quality of life regarding symptoms and impact of symptoms, sexual function, and costs.

### Randomization

After giving informed consent, patients will be randomized in a 1:1 ratio to either MM or SSH, with use of dynamic block randomisation with blocks of 2, 4 or 6. Randomisation will be done by gynaecologists or research nurses using the online software Castor (version 2018.3.11, Castor Electronic Data Capture, Amsterdam, The Netherlands). Due to the nature of the investigational treatments, blinding is not possible. Participating gynaecologists and investigators will not be able to access the randomization sequence. All analyses will be performed in a blinded fashion.

### Sample size calculation

The sample size calculation was based on the expected comparability between the two techniques regarding the success composite of recurrent signs and symptoms of POP after two-years follow-up. We expect a success rate of 89% for both SSH [13] and MM, two years after the intervention. The actual treatment group proportion (SSH) was set at 89% with a non-inferiority margin of 9%, assuming SSH to be below 80% under the null hypothesis of inferiority. The 9% non-inferiority margin was motivated by the margins used in two other large national studies SAVE-U (7%) [13] and PEOPLE study (10%) [29]. Based on a power of 80% and the significance level of the test (α) targeted at 0.025, sample sizes of 193 per group need to be included in the study. With an expected loss to follow-up of 10% [27], a total of 424 women are needed. The sample size calculation was performed with PASS (version 15.0.7, NCSS statistical software, Kaysville, USA).

### Data collection

All women will undergo gynaecological examination including POP-Q which must be done in 45 degrees supine position. All measurements performed during pre-operative and follow-up outpatients visits, as well as the operation report, will be systematically recorded in an electronic Case Report Form in Castor. All data will be kept anonymous where possible. All participants will be assigned an identification code based on number of the hospital and number of inclusion. A list linking the code to the subject will be kept safe by the local investigators. Personal data will be stored for a maximum of 15 years in participating centres.After randomization patients will be sent an e-mail with a link to the pre-operative questionnaires in Castor. If the subject prefers paper questionnaires, written informed consent is needed to get insight in the postal address of the subject. Both groups will fill in the same questionnaires. The pre-operative questionnaire consists of questions on baseline characteristics, and standardized, validated questionnaires about quality of life (EQ5D-5 L: EuroQol-5D-5 L) [30], disease specific quality of life regarding symptoms (Pelvic Floor Disability Index-20) and the impact of those symptoms (Pelvic Floor Impact Questionnaire-7) [31], sexual function (Pelvic organ prolapse Incontinence Sexual Questionnaire-IR) [32], and the validated cost utility questionnaires of the institute for Medical Technology Assessment (iMTA) (PCQ: Productivity Cost questionnaire and MCQ: Medical Consumption Questionnaire) [33]. After surgery, the patients will visit the hospital at 6 weeks, 12 months and 24 months (see Table 1). During the follow-up specific history taking and gynaecological examination including POP-Q will be done. The POP-Q at 12 and 24 months will be performed by another researcher than the operating gynaecologist. Reimbursement of travel expenses is available to minimize no shows. At 6 months, 12 months and 24 months patients will receive abovementioned questionnaires and an additional disease specific questionnaire (Patient Global Impression of Improvement). At 12 weeks and 9 months patients receive the PCQ, MCQ and EQ5D-5 L; these extra moments are incorporated to prevent recall bias. Reminders will be sent after two weeks in case of non-completion of questionnaires. The duration of the follow-up period is set at 2 years because the majority of recurrences after POP surgery will occur in these first two years [34, 35]. Women will be asked for permission to ask them to participate in a longer follow-up study in case this seems valuable after the two year analysis.

**Table 1 Tab1:** Schematic overview of follow-up

Measurement	Follow-up moment						
	Pre-op	6 wks	12 wks	6 months	9 months	12 months	24 months
Outpatient visit including POP-Q		x				x	x
Baseline characteristics	x						
EQ5D-5 L	x		x	x	x	x	x
PDFI-20, PGI-I, PFIQ-7, PISQ-IR	x^a^			x		x	x
PCQ and MCQ			x	x	x	x	x

^a^without PGI-I

## Statistical analysis

### Data analysis

Regarding the primary outcome, the null hypothesis entails that the success rate of SSH is inferior by a margin of 9% compared to MM. If the lower limit of the 95% confidence interval does not exceed the margin of − 9%, the null hypothesis is rejected, and we will consider SSH to be non-inferior to MM. The statistical analysis will be performed both by the intention to treat (ITT) and per protocol (PP) principle. This means that non-inferiority has to be demonstrated in both the ITT and PP analysis to declare non-inferiority of SSH compared to MM. The treatment effect will be expressed as relative risk with a 95% confidence interval.

For other (secondary) outcomes, summaries of continuous data will be presented as mean ± standard deviation or median and (interquartile) range depending on their distribution. Categorical data will be presented as frequencies. When appropriate, differences between groups will be analysed using the Student’s t test or Mann-Whitney test for continuous data. Comparisons with categorical data will be analyzed using the Chi-square test of the Fisher’s exact test.

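### The primary non-inferiority rule is worded the wrong way round: read literally, it declares SSH non-inferior when the lower confidence limit is at or below −9%

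*Protocol article*

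**What the plan says.** All references are to the protocol article.

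- **Outcome measures** fixes the orientation of the endpoint: "The primary outcome will be success after two years follow-up". Higher is better.
- **Data analysis**, null hypothesis: "the null hypothesis entails that the success rate of SSH is inferior by a margin of 9% compared to MM".
- **Data analysis**, decision rule, in the next sentence: "If the lower limit of the 95% confidence interval does not exceed the margin of" minus 9%, then "the null hypothesis is rejected, and we will consider SSH to be non-inferior to MM". The margin is printed with a minus sign.
- **Data analysis** also requires the criterion to be met in both the ITT and the PP analysis. The only effect measure it names is the relative risk.
- **Sample size calculation** puts the null in the same direction: "assuming SSH to be below 80% under the null hypothesis of inferiority". The planning assumption is "We expect a success rate of 89% for both SSH [13] and MM, two years after the intervention", and the error rates are given by "Based on a power of 80% and the significance level of the test (α) targeted at 0.025".

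**The concern.** For a success outcome compared as SSH minus MM, non-inferiority is shown when the whole 95% interval lies above −9 points, so the lower limit must be greater than −9. The printed sentence rejects the null when the lower limit is not greater than −9. In that case the interval contains the margin or lies wholly below it, and the null cannot be rejected.

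This is the trial's only confirmatory decision rule. The Implementability and Discussion sections intend the result to feed national guideline recommendations and possibly the de-implementation of one operation. A pre-specified rule for such a decision should not need the reader to guess which side of the margin counts as success.

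**Working it through.** **Inputs.** From Sample size calculation: success 89% in both arms, margin 9 points, alpha 0.025, power 80%, 193 per group. From Data analysis: a 95% interval and its lower limit. Assumption: a Wald interval for the difference, because that section names no interval method.

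**Step 1: reproduce the planned sample size under the conventional rule (lower limit > −9 points).**

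n per group = (z₀.₉₇₅ + z₀.₈₀)² × [p(1 − p) + p(1 − p)] / margin²
= (1.960 + 0.842)² × (2 × 0.89 × 0.11) / 0.09²
= 7.849 × 0.1958 / 0.0081 = 189.7, so 190.

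The plan states 193, within 2% of this. A Farrington–Manning calculation gives 202. The plan's figure therefore belongs to the conventional direction.

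**Step 2: see whether the literal direction could have produced that figure.** With equal arms, the normal approximation gives these probabilities of declaring non-inferiority:

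| n per arm | Lower limit > −9 | Lower limit ≤ −9 (literal) |
|---|---|---|
| 190 | 80.1% | 19.9% |
| 193 | 80.7% | 19.3% |
| 212 | 84.2% | 15.8% |

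Under the literal rule the chance of a positive result with equal arms falls as the trial grows. It cannot be the rule behind a calculation with 80% power.

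**Step 3: operating characteristics at the planned size.** Exact binomial enumeration of all outcome pairs, 193 per arm, MM success 89%:

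| True SSH success | Lower limit > −9 | Lower limit ≤ −9 (literal) |
|---|---|---|
| 89% (equal) | 80.9% | 19.1% |
| 80% (on the margin) | 2.7% | 97.3% |
| 75% | 0.06% | 99.9% |

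The middle column matches the planned 80% power and is close to the 0.025 alpha; the small excess at 2.7% comes from the Wald approximation. These figures are for one analysis set. Requiring ITT and PP together can only lower the probability of a declaration.

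**Step 4: three example results, 193 per arm.** The interval is d ± 1.96 × √[p₁(1 − p₁)/193 + p₂(1 − p₂)/193].

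| SSH v MM successes | Difference (points) | 95% CI (points) | Correct direction | Literal text |
|---|---|---|---|---|
| 172 v 172 | 0.0 | −6.2 to +6.2 | non-inferior | not shown |
| 165 v 172 | −3.6 | −10.3 to +3.0 | not shown | non-inferior |
| 150 v 172 | −11.4 | −18.7 to −4.1 | not shown | non-inferior |

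In the third row SSH is significantly worse, yet the literal text calls it non-inferior. The second row is the realistic borderline case in which the wording could be disputed.

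**Step 5: scale.** The margin is an absolute difference: 89% − 9% = 80%, as the sample size section has it. A relative risk and its confidence limits cannot be negative, so they cannot be set against −9%. The sentence does not name the quantity whose interval is meant.

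**The case against.** The strongest reply is that the meaning is plain. To exceed a limit is often used loosely for going beyond it, and for a lower confidence limit and a negative margin, going beyond means falling below −9%. On that reading the sentence is the standard rule. The neighbouring null, the 80% null rate, the alpha and power, and the sample size all point to that one direction. Most of this stands: it establishes what the authors intended. It does not make the printed sentence correct, and no other sentence in the article states the rule the right way round.

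Three stronger readings should be resisted.

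- A reader might infer that the trial will run with a false-positive rate near 97%. The documents do not support this. It would need an analyst to apply the sentence literally against the null in the same paragraph. The figures measure the literal wording and do not predict what will be done.
- A reader might infer that the direction of the difference is left open, so the sentence cannot be repaired from context. It is not written as a formula, but a null on the success rate of SSH relative to MM, a negative margin and the use of the lower limit together imply SSH minus MM on the success scale.
- A reader might infer that a separate rule for calling SSH inferior is needed. The protocol has none, and correcting this sentence does not require one.

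**Conclusion.** The point holds as a wording error in the primary decision rule, with an intention that can be recovered from the context. It is not a flaw in the design, margin, alpha, power or sample size. As printed, the rule is the reverse of the one the plan's own null and sample size require. On the literal reading only, it would declare non-inferiority about 97% of the time with SSH at 80% and about 19% of the time at equality, against 2.7% and 81% in the correct direction. These values assume 193 evaluable women per arm, MM success of 89%, a Wald interval and a single analysis set. Because this is the only confirmatory threshold and the correction costs nothing, it should be made before the two-year data are analysed.

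**What to change.** Replace the decision sentence in Data analysis with:

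> The null hypothesis is rejected and SSH is declared non-inferior only if the lower limit of the two-sided 95% confidence interval for the absolute difference in success proportions (SSH minus MM) is greater than −9 percentage points, in both the ITT and the PP analysis; otherwise non-inferiority has not been shown.

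Add that the relative risk may be reported as a further description of the effect but is not compared with the −9% margin. Use the same sentence in the statistical analysis plan, if there is one.

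The cost is one sentence of text. The number of women, the data collected and the conduct of the trial do not change.

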### Other study parameters

Subgroup analyses are planned to investigate the effects of the POP surgery with MM versus SSH in the following pre-specified subgroups: age, menopausal status, sexual activity, POP-Q stage, cervical elongation, concomitant vaginal repair and symptoms.

A prognostic marker analysis will be performed to assess which baseline characteristics of the women have prognostic value and/or can be used as treatment selection markers. Missing covariates will be imputed as appropriate (with solid logical strategy). We will use multiple imputation based on other baseline variables that are associated with higher or lower values of the variable that is imputed. We will do sensitivity analyses to evaluate the difference between imputed and non-imputed variables. All analyses will be performed with IBM SPSS Statistics (version 25, Armonk, New York, United States).

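### The per-protocol analysis can veto non-inferiority although surgeons' judgement during the operation can shape its membership, and the article names only a relative risk, with no baseline variables, for the primary outcome

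*Protocol article*

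**What the plan says.** The Data analysis section gives ITT and PP equal decisive weight: "non-inferiority has to be demonstrated in both the ITT and PP analysis to declare non-inferiority of SSH compared to MM". It sets the lower limit of a 95% confidence interval against a margin of -9%, then states: "The treatment effect will be expressed as relative risk with a 95% confidence interval". No baseline variables are mentioned for this comparison.

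The Intervention section describes how a woman can come to depart from her allocation: "Allocated interventions will only be modified or discontinued in case the operating gynaecologist believes this is necessary during operation". Such changes are registered. The Randomization section says "Due to the nature of the investigational treatments, blinding is not possible", and adds "All analyses will be performed in a blinded fashion".

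The Other study parameters section lists subgroups ("age, menopausal status, sexual activity, POP-Q stage, cervical elongation, concomitant vaginal repair and symptoms"). It separately plans a prognostic marker analysis of baseline characteristics, without naming them. Neither is linked to the primary comparison.

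**The concern.** Randomisation protects the ITT comparison. It protects PP only if leaving the PP set is unrelated to prognosis, or related to it in the same way in both arms. Here departures are decided after randomisation, by a surgeon who knows the allocation and sees the anatomy.

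The article gives some reason to expect the two arms to differ. The Background suggests that MM may suit an elongated cervix better than SSH does. The section on study population states the authors' belief that, beyond a given position of point D, the sacro-uterine ligaments give too little support, so that SSH would serve the patient better. These remarks concern choice before surgery, but the same beliefs could prompt a surgeon to abandon one operation and not the other. Blinding the analysis does not undo selection made in theatre.

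Two things are at stake. If poor-prognosis women leave MM, its PP success rate rises and PP can refuse a conclusion that is true. If they leave SSH, PP becomes easier to pass and adds little to ITT.

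**Working it through.** **Inputs from the article** (Sample size calculation, Data analysis): "We expect a success rate of 89% for both SSH [13] and MM, two years after the intervention"; margin 9 points; alpha 0.025, taken as one-sided to match the lower limit of a 95% CI; power 80%; 193 per group; 424 in total.

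**Assumptions** (the article gives no departure figures): f = share of an arm leaving PP; s = success those women would have had. All calculations use 193 evaluable women per arm and a Wald interval on the risk difference, the scale on which a -9% margin makes sense.

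**1. The plan's own figure.** n = (1.960 + 0.842)² × 2 × 0.89 × 0.11 / 0.09² = 7.85 × 0.1958 / 0.0081 ≈ 190 per group, within 3% of 193. The total follows from 193 × 1.10 = 212.3, and 2 × 212 = 424.

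**2. ITT power at 193 per arm.** SE = √(2 × 0.89 × 0.11 / 193) = 0.0319. Power = Φ(0.09/0.0319 − 1.96) = 80.7%.

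**3. Non-selective loss of 5% in each arm.** n = 193 × 0.95 = 183.4, SE = 0.0327, PP power 78.6%. In simulated trials both analyses pass in about 77%.

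**4. The same 5% loss, but women leaving MM have s = 0.70.** The success rate in those who stay is (0.89 − f × s)/(1 − f).
- MM in PP: (0.89 − 0.05 × 0.70)/0.95 = 0.900. SSH in PP stays at 0.89.
- SE = √[(0.89 × 0.11 + 0.90 × 0.10)/183.4] = 0.0320.
- PP power = Φ((0.09 − 0.01)/0.0320 − 1.96) = 70.5%. By simulation, both analyses pass in about 70%.

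The cost of selection is therefore about 7 points (77% to 70%). The rest of the fall from 81% comes from the smaller sample and from having to pass two analyses.

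**5. How this varies with the assumptions** (equal true success of 89%; simulated chance of passing both).

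| Departures | Both pass |
|---|---|
| MM only, 2% at s = 0.60 | 76% |
| MM only, 5% at s = 0.60 | 67% |
| MM only, 10% at s = 0.60 | 48% |
| SSH only, 5% at s = 0.60 | 81% |
| Both arms, 5% at s = 0.70 | 78% |
| Both arms, 8% at s = 0.60 | 78% |

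Only selection concentrated in MM does harm here.

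**6. At the null (SSH 80%, MM 89%).** If 5% of SSH women leave PP with s = 0.50, SSH in PP becomes (0.80 − 0.025)/0.95 = 0.816. PP alone then passes in 6.7% of simulated trials. Both analyses pass in 2.6%, against about 2.7% for ITT alone. With 10% leaving at s = 0.40, PP alone passes in about 25% and both in 2.7%. The safeguard is weakened, but the error rate of the decision does not exceed that of ITT.

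**7. Precision from adjustment in ITT.** If baseline variables explain a share R² of the variance, SE becomes 0.0319 × √(1 − R²). Power is 81.8%, 82.6% and 84.6% for R² = 0.03, 0.05 and 0.10. These R² values are assumed.

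**The case against.** Requiring both analyses is a common and conservative rule for non-inferiority, and is not an error. The article also restricts departures: eligibility excludes women for whom the authors think MM unsuitable, surgeons need minimum experience of each technique, master classes were held, and changes are registered. Departures may be few, and similar selection in both arms largely cancels (step 5). All of this stands, and it limits the likely size of the problem.

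A reader might infer that selective exclusions could produce a false non-inferiority claim. The decision rule excludes this: ITT must also pass, so PP can only veto (step 6).

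A reader might also infer that an unadjusted analysis is the whole plan. The article does not say that the relative risk is unadjusted, or that PP will have no further analysis. The definition of the PP set, the listing of exclusions and sensitivity analyses may stand in a full protocol or SAP that is not shown, and their absence here is no finding.

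Nor does the article nominate the proposed covariates as prognostic. The list in Other study parameters is a subgroup list, and the prognostic marker sentence names no variables. The list shows only which characteristics the authors intend to use in subgroup analyses.

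Finally, adjustment for baseline variables cannot remove selection on what the surgeon sees only during the operation. That is correct. How much bias adjustment would remove in PP has not been quantified.

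**Conclusion.** The point holds in a limited form. The article gives a veto to a comparison whose membership can depend on unblinded judgement in theatre, and the only effect it names for the primary outcome is a relative risk, while the margin is a difference of 9 points. Departures that are prognostic and concentrated in MM would lower the chance of a correct non-inferiority conclusion: from about 77% to 70% with 5% departing in each arm and 70% success among those leaving MM, and further under heavier selection. Selection concentrated in SSH would weaken PP as a check without raising the joint error above the ITT level. Every departure share and success rate is an assumption, so the true size is unknown and may be small. What justifies a change is that a better primary estimate is available at almost no cost.

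**What to change.** In Data analysis, make the primary estimate for both ITT and PP the risk difference standardised from a logistic model with a short list of baseline variables, for example age, menopausal status, POP-Q stage and cervical elongation. Fix the list before unblinding. Compare the 95% CI (delta method or bootstrap) with the -9 point margin, and report the crude risk difference and the relative risk as supportive. Keep the requirement that both analyses pass. A PP sensitivity analysis weighted by the inverse probability of staying in the PP set is optional.

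The cost is a few lines of wording and a little programming. No treatment, visit or sample size changes. The gain is less measured confounding in PP and modestly more precision in ITT; selection on unmeasured findings during the operation remains and should be acknowledged when the PP result is interpreted.
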